## Abstract

**Background::**

Cardiovascular diseases are highly prevalent and represent leading causes of morbidity worldwide, including in Central Europe. Cardiac rehabilitation (CR) is an effective method of secondary prevention, but utilization is low. Barriers to CR use in the Czech Republic are not well-characterized, and therefore we propose a protocol to translate and validate the cardiac rehabilitation barriers scale (CRBS).

**Methods::**

In this multi-method study, we translated and cross-culturally validated the CRBS to Czech (CRBS-CZE) first through the following main steps: professional translation, reconciliation/harmonization, and cross-cultural adaptation, and piloting in 50 cardiac patients. A prospective study will be undertaken to psychometrically-validate the CRBS-CZE, where 300 to 600 cardiac inpatients eligible for phase II/outpatient CR will be recruited. Consenting participants will be informed about the CR program and their sociodemographic, clinical characteristics, and the CRBS-CZE administered. Factor analysis will be performed with oblique rotation, factors will be extracted based on eigenvalues, the examination of the scree plot, and factor loadings. The internal reliability of the total scale and subscales will be assessed with Cronbach alpha. Overall CRBS scores will be compared by patient characteristics such as sex, socioeconomic indicators, risk factor burden, and travel time to investigate content validity. Their CR enrollment, adherence (% of 24 prescribed sessions attended), and completion will be tracked. The second administration of CRBS-CZE will be undertaken in patients at 3 weeks after enrollment. To test criterion validity, *t* tests and Pearson correlation (for adherence) will be used to determine the association of these utilization indicators with CRBS scores.

**Results::**

The translated version was considered by 2 bilingual CR experts. Some revisions and example additions were made to the items. Upon piloting with patients, some further edits were made. No additional barriers were raised.

**Discussion::**

Through this study, a reliable and valid means of assessing patient's CR barriers will be established. Results will be used to identify ways to help patients overcome barriers to CR utilization.

## Introduction

1

Cardiovascular diseases (CVDs) are the leading causes of death in the world, and are a significant burden in Central Europe in particular.^[1]^ These many cardiac patients are at increased risk for recurrent events.^[2]^ For example, CVDs are the most common reasons for hospitalization in the Czech Republic, as well as are common sick leave and disability causes.^[3]^ According to the Czech Statistical Office, 25.4 billion CZK was spent on CVDs treatment in 2016, which was 13.6% of all health care expenditures that year.^[4]^ These diseases also represent a severe socioeconomic problem for patients and their families. This is unfortunate, given, according to the World Health Organization, that nearly 75% of recurrent cardiovascular events may be prevented.^[5]^ Indeed, cardiac rehabilitation (CR) is an effective secondary preventive model of care to mitigate this burden.^[6]^ However, CR is grossly under-utilized worldwide, including in Central Europe.^[7]^

The reasons for under-utilization are well-established in high-resource settings such as Western Europe and North America, consisting of factors at the health system, provider, and patient levels.^[8–10]^ A recent review; however, reveals just how few studies have explored these barriers outside of these settings, even though the burden of CVDs is so much higher here.^[11]^

Validated scales such as the cardiac rehabilitation barriers scale (CRBS), to assess reasons for under-utilization are available in the English language.^[12]^ Despite being self-reported by patients, they can validly capture barriers at these multiple levels. Studies reveal key barriers include lack of perceived need/awareness, distance to center, and work conflicts. These are amenable to relatively simple mitigation efforts, and hence barrier identification in patients is essential to promoting their access and participation. The CRBS has now been translated into 14 languages.^[13]^ Studies in non-Western settings do reveal different barriers, barriers which again are ripe for mitigation, bolstering the importance of measuring these barriers in these settings.^[11]^

Barriers to CR participation in the Czech Republic are still unknown or not adequately described, despite this great need for CR as outlined above, as in the whole Central Europe. The aim of the study is first to translate and cross-culturally adapt CRBS to Czech (CRBS-CZE), and then psychometrically-validate the translation. The study shall include an assessment of the structure of factors, internal reliability as well as validity (design and criterion).^[14]^ The second aim then is to identify the key barriers which prevent patients from entering phase II of CR (outpatient). Furthermore, we will describe the degree of CR utilization in the program, namely, enrollment, adherence, and completion.^[15]^

## Methods

2

### Design and ethical considerations

2.1

This is a multi-method study, first involving a translation and cross-cultural validation process for the CRBS, and second a prospective, observational study to psychometrically-validate it. The project respects the World Medical Association Declaration of Helsinki on ethics in medical research and received approval by the Ethical Committee of the University Hospital (UH) Brno, Czech Republic. This study is registered at the Australian New Zealand Clinical Trial Registry with registration number: ACTRN12619001181190. Data will be password-protected so that only the research team can access it. Personal information will be processed and backed up according to the current General Data Protection Regulations.

### Setting

2.2

The prevalence of cardiovascular risk factors in the Brno region is high.^[16]^ This study will be undertaken at the UH Brno of the Czech Republic. Approximately 1000 patients are hospitalized in the Department of Internal Cardiology Medicine, where recruitment will take place annually. The physicians in the Department have an association with the CR program and are generally supportive of patients referrals.

The institution also has an outpatient CR program. It is a comprehensive program consisting of exercise and education of lifestyle, and it is delivered dominantly by physiotherapists. Indicated patients have to complete cardiopulmonary exercise test before CR enrollment and post-program. There is practically no waiting list, and patients commence CR approximately 4 to 12 weeks post-discharge, depending on their clinical status and preferences. It involves 3 sessions a week for 2 months (total 24 trainings). The health insurance company completely covers the CR program. There could be a problem with parking because of a few places.

### Translation and cross-cultural adaptation

2.3

We aimed to follow best practices to ensure the translation was accurate, high-quality, and culturally-relevant.^[17–20]^ The following steps were undertaken: preparation, translation, reconciliation/harmonization, and cultural adaptation, piloting, and finalization. For preparation, permission was obtained from [name] to translate the English-language scale, needed experts were invited to the project (professional translator, CR experts), and the target audience was finalized (patients of UH Brno, Czech Republic, indicated for phase II/outpatient CR). In the second step, the source version was translated by a professional translator whose native language was Czech. Next, 2 bilingual CR experts reviewed the translation, considered any conceptual discrepancies with the English version, and identified any wording that might not be culturally applicable. The revised version was then piloted in 50 target patients who had not been to CR as well as CR participants using a think-aloud protocol and follow-up semi-structured interview regarding clarity, relevance, and omissions. The expert team considered all the information from the pilot and finalized the CRBS-CZE.

### Psychometric validation

2.4

Eligible patients in the Department of Internal Cardiology Medicine will be approached from January 2020 for 1 year. Consenting patients will be informed about CR and referred. A physiotherapist will provide a questionnaire to the participants assessing their characteristics as well as the CRBS-CZE and will assist them in completion as needed. Thus all data will be secured via self-report, interview with patients, measurement, and will also be extracted from charts where available. Patients’ enrollment, session attendance, and completion of the program will be tracked in the CR charts (this too will be extracted for the study 2 months later). At 3 weeks after enrollment participated, patients will complete CRBS-CZE for the second time. A flowchart of the study protocol is shown in Figure 1.

**Figure 1 F1:**
[figure not shown]
Flowchart of the study protocol.

### Participants

2.5

Adult coronary artery disease (CAD) patients meeting the criteria for phase II of CR will be recruited (primo manifestation of CAD, acute coronary syndrome, angina pectoris, percutaneous coronary intervention, coronary artery bypass graft, heart failure, arrhythmia, valve defect). Exclusion criteria were as follows: no significant acute cardiovascular risk, no implanted cardioverter-defibrillator or pacemaker, no orthopedic or neurological disability impeding ability to exercise, no mental condition precluding participation (schizophrenia, advanced dementia).

The rule of thumb for factor analysis is 10 participants per variable (at least 5), which would be 210 patients. The expected number of research group patients is 300 to 600 respondents. This is also a reasonable sample size to establish the validity of the translation, as demonstrated in previous CRBS translations.^[21,22]^

### Sample characteristics

2.6

The sociodemographic and clinical characteristics of the participant will be obtained. Some of these variables were also used to test the content validity of the CRBS-CZE, given many represent or are related to CR barriers or groups that are less likely to participate. Sociodemographic characteristics will include age, sex, marital status, highest educational attainment, income, work status (including shift work, degree of occupational exertion for those employed). Clinical characteristics will include diagnosis, risk factors (anthropometrics, blood pressure, lipids, diabetes), heart-healthy behaviors (physical activity, mins of moderate-vigorous intensity activity/week; tobacco use; harmful use of alcohol, number of standard drinks), and psychosocial well-being (stress, visual analog scale, 1–10; depression/anxiety, diagnosed or subjective). Also, the time to travel to the center will be assessed.

### CRBS

2.7

This scale evaluates patients’ perception of the degree to which patient, provider, and health system-level barriers affect their CR enrollment and participation (all items applicable to enrollers and non-enrollers alike). The English version consists of 21 items (barriers), related to 4 subscales – healthcare system factors, logistical barriers, work/time conflicts, comorbidities/functional status (although some translations consist of 5 subscales). These items are rated on a 5-point Likert scale (1 – strongly disagree, 5 – strongly agree). Higher scores indicate greater barriers to CR. There is also an open-ended item at the bottom where patients are asked to report any additional factors. Criterion validity has been established in the English version and many of the translations, demonstrated by significant differences in CRBS scores by CR use.^[21,23]^

Where participants completed >80% of the items, a mean total score will be computed. Subscale scores will also be computed based on the results of the factor analysis.

### Outcomes for validating the CRBS-CZE and CR utilization

2.8

Patients attending at least 1 training session will be considered enrollers by 12 weeks post-discharge. The rest of them will be qualified as non-enrollers. Patients attending >75% of total training will be marked as completers and <75% of total attendance as non-completers. This will be used to test criterion validity. As outlined above, differences in barrier scores by some patient characteristics will also be assessed to investigate content validity; these will include sex, age, travel time, indication (primo manifestation of CAD vs chronic problems), socioeconomic indicators, and risk factor burden.

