### Analysis

2.9

The process of reconciliation/harmonization and cultural adaptation, piloting, and finalization will be documented in detail, and any associated revisions to items specified. For the psychometric validation, Statistica TIBCO (Software Inc, Palo Alto, USA) will be used, and *P* < .05 will denote statistical significance. First, data to characterize the sample will be processed via descriptive statistics – mean, standard deviation, as well as frequencies and percentages. We will consider the completeness of the scale by using content analysis to code any additional barriers reported by respondents. We will assess factor structure with maximum likelihood factor analysis with oblique rotation. Factors with Eigen values >1 will be extracted according to the Kaiser–Guttman criterion. The scree plot will also be considered to confirm the appropriate number of factors. Factor loadings >3 will be interpreted in terms of subscale determinations. To evaluate the internal reliability of CRBS-CZE, we will use Cronbach alpha. To compare barriers by utilization indicators to test criterion validity, we will use a *t* test and Pearson correlation, as applicable. To test construct validity, differences in CRBS total scores will be compared by the sociodemographic and clinical characteristics outlined above, using the same 2 tests as applicable. Finally, interpretation of highest subscale and item scores will ensure to identify key barriers in this setting.

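### Deaths and new clinical ineligibility after the inpatient score are coded as non-enrollment or non-completion, which blurs the criterion-validity test; record the reason and add a sensitivity analysis

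*Protocol article*

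**What the plan says.** Section 2.8 defines the criterion variable: "Patients attending at least 1 training session will be considered enrollers by 12 weeks post-discharge", followed by "The rest of them will be qualified as non-enrollers". The two groups are exhaustive. The same section splits participants into completers and non-completers at 75% of sessions, again without regard to why sessions were missed, and says of the classification: "This will be used to test criterion validity".

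Section 2.9 names the tests: "To compare barriers by utilization indicators to test criterion validity, we will use a *t* test and Pearson correlation, as applicable". The Abstract assigns the correlation to adherence, the percentage of the 24 sessions attended.

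On timing, the Abstract and section 2.4 have participants recruited and scored while in hospital. Section 2.2 says "patients commence CR approximately 4 to 12 weeks post-discharge, depending on their clinical status and preferences". It adds a step before entry: "Indicated patients have to complete cardiopulmonary exercise test before CR enrollment and post-program". The Introduction says of the population: "These many cardiac patients are at increased risk for recurrent events".

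**The concern.** Weeks pass between the score and the start of the program, in a population that the article itself describes as prone to further events. Section 2.2 names two separate drivers of when a patient starts, clinical status and preference. Section 2.8 merges them in the outcome.

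A participant who dies in week 3, or who develops a new medical reason not to train, is grouped with one who stayed away because of distance or work. An enroller whose program is stopped by a clinical event becomes a non-completer and has low adherence.

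The criterion tests are meant to show that perceived barriers separate users from non-users. An event that arises after scoring and removes the possibility of attending says little about that, but all such participants land on one side of the comparison. The difference in mean score then reflects barrier-related non-use plus an unknown contribution from the course of the disease. Without a recorded reason, a reader cannot tell the two apart.

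**Working it through.** **Plan's own figure.** The only sample-size figure is for the factor analysis: 21 items x 10 = 210, which reproduces. No effect size, enrollment rate or event rate is given for the enroller comparison, so what follows illustrates the mechanism and does not estimate its size.

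**Assumed inputs.** 400 participants (within the 300 to 600 expected in section 2.5) and 160 enrollers, hence 240 coded as non-enrollers. Of the 400, 5%, 10% or 15% become unable to start: u = 20, 40 or 60. The remaining non-enrollers number N = 240 - u.

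**Formula.** Set the enrollers' mean score to 0, the mean of the N able non-enrollers to D, and the mean of the unable to m. The share of D that the planned comparison retains is

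R = [N + u x (m/D)] / 240.

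**Base case: the unable score like all able participants on average.** Then m/D = N/(400 - u).

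| u | Share of non-enrollers (u/240) | R | Shrinkage |
|---|---|---|---|
| 20 | 8.3% | [220 + 20 x 220/380]/240 = 0.965 | 3.5% |
| 40 | 16.7% | [200 + 40 x 200/360]/240 = 0.926 | 7.4% |
| 60 | 25.0% | [180 + 60 x 180/340]/240 = 0.882 | 11.8% |

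**Direction.** The formula can be written R = 1 - (u/240)(1 - m/D).

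- m = 0 (the unable score like enrollers): R = 0.917, 0.833, 0.750.
- m = D (they score like able non-enrollers): R = 1, no distortion.
- m = 1.5D (they score higher still): R = 1.042, 1.083, 1.125, so the difference is inflated.

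The sign depends on whether the unable score below or above the able non-enrollers, which the documents do not settle.

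**Power under the dilution case m = 0.** Assume 300 participants, half enrolled, a true difference of 0.3 SD and two-sided alpha 0.05. The percentages below are the unable as a share of non-enrollers.

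| Unable | Power, unable kept as non-enrollers | Power, unable left out |
|---|---|---|
| 0% | 74% | 74% |
| 10% | 65% | 72% |
| 20% | 55% | 69% |
| 30% | 44% | 66% |

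In this case, leaving the group out costs little power compared with keeping it in.

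**Enrollment rate, base inputs.** All participants: 160/400 = 40%. Those still able to start: 160/380 = 42.1%, 160/360 = 44.4%, 160/340 = 47.1%.

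**The case against.** Several counter-arguments have force.

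- **The exercise test.** A reader might infer that patients who fail the test are shut out and then miscoded. Section 2.2 only requires the test to be completed; it describes no pass mark and no refusal of entry. Not attending the test may itself result from a barrier. This stands, and such patients are properly non-enrollers.
- **Poor function belongs to the construct.** The scale covers patient, provider and health-system barriers and has a subscale for comorbidities and functional status (section 2.7). That subscale should predict non-entry through poor function. It would be wrong to say that it only looks valid because it marks severity, or that all clinically limited patients are uninformative. This stands. The point is confined to death and clinical ineligibility arising after the score.
- **Understated rates.** A reader might infer that the enrollment and completion rates are wrong. Attendance among all referred participants is a legitimate measure of utilization, which section 1 sets out to describe. The rate among those able to start answers a different question.
- **Restricting the main test.** Conditioning on being alive and eligible selects on a status that arises after the score, depends partly on clinical judgment and may be related to the comorbidity items. That can bring its own bias, so the restriction is better placed as a sensitivity analysis.
- **Few early events.** Section 2.5 selects patients who meet the criteria for outpatient rehabilitation, which plausibly lowers early inability. It cannot exclude later events.
- **A condensed article.** Coding of reasons is often left to a fuller document, and the flowchart (Figure 1) was not available for this check. But the finding does not rest on an absent field. Section 2.8 states a rule that already assigns these participants.

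**Conclusion.** The point holds in a limited form. Followed as written, section 2.8 codes death and clinical ineligibility arising after the inpatient score as non-enrollment, or as non-completion when the program has begun, and section 2.9 tests criterion validity on those groups. No figure in the article is contradicted.

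A reader might conclude that criterion validity is definitely biased. The documents do not support that, because they give no rate of death or new ineligibility, no enrollment rate and no scores for the affected patients. The shrinkage of about 3.5% to 12% rests wholly on the assumed 400 participants, 160 enrollers and 5% to 15% unable with average scores. It grows if the unable score like enrollers and turns into inflation if they score above the other non-enrollers. What is established is that the planned result cannot be read cleanly without knowing why participants did not attend. This justifies a small addition to the plan and no change to the main comparison.

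**What to change.** At the chart extraction already planned in section 2.4, add one coded field for the reason for no session or an early stop, with three values: died or newly clinically ineligible, as documented by the treating team; did not take up or dropped out; unknown. State that poor function present at scoring and non-attendance at the exercise test do not by themselves fall in the first group.

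Keep the all-participant enrollment and completion comparisons and rates as they are. Add a prespecified sensitivity analysis that repeats the criterion-validity tests and the enrollment rate without the first group, report the number in each reason category, and interpret criterion validity on both results.

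The cost is one extra field, slightly fewer non-enrollers in the sensitivity analysis, and some incompleteness. Non-enrollers have no session record, and events outside this hospital may not reach its charts, so the unknown category could be sizeable and should be shown.

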### Analysis

2.9

The process of reconciliation/harmonization and cultural adaptation, piloting, and finalization will be documented in detail, and any associated revisions to items specified. For the psychometric validation, Statistica TIBCO (Software Inc, Palo Alto, USA) will be used, and *P* < .05 will denote statistical significance. First, data to characterize the sample will be processed via descriptive statistics – mean, standard deviation, as well as frequencies and percentages. We will consider the completeness of the scale by using content analysis to code any additional barriers reported by respondents. We will assess factor structure with maximum likelihood factor analysis with oblique rotation. Factors with Eigen values >1 will be extracted according to the Kaiser–Guttman criterion. The scree plot will also be considered to confirm the appropriate number of factors. Factor loadings >3 will be interpreted in terms of subscale determinations. To evaluate the internal reliability of CRBS-CZE, we will use Cronbach alpha. To compare barriers by utilization indicators to test criterion validity, we will use a *t* test and Pearson correlation, as applicable. To test construct validity, differences in CRBS total scores will be compared by the sociodemographic and clinical characteristics outlined above, using the same 2 tests as applicable. Finally, interpretation of highest subscale and item scores will ensure to identify key barriers in this setting.

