## Discussion

3

CR participation is associated with reductions of recurrent cardiovascular events and mortality, decreased hospitalization, and improvements in quality of life.^[6,24,25]^ Despite these benefits and recommendations to refer patients, utilization of CR is low.^[26–28]^ Older people, women, patients with comorbidities, unemployed and single persons, less educated people, those with lower income, and those that live farther from CR facilities have even lower enrollment and adherence to center-based training programs, despite in many cases, greater need.^[28,29]^ Studies demonstrating the effectiveness of CR in the Czech Republic already exist, even in Brno, but there are no studies about utilization and barriers to CR. Given the burden of CVDs, this work will fill this critical gap.^[30]^

Low utilization of CR is a global problem. Thus, strategies to improve utilization of rehabilitation programs have been developed and tested and now demonstrated rigorously to work in high-resource settings.^[31,32]^ Once the specific, critical barriers in this setting are identified, we will undertake more research to determine which of these strategies might be most relevant and effective here. We will conduct further research to establish specific, implementable materials and protocols to overcome the barriers and test them to ensure there is an evidence base to confirm effectiveness. We assume that one of the most critical barriers to CR in the Czech Republic will be the long commuting time to training facilities. One alternative is the use of telemedicine technology. CR delivered using this technology appears to be at least as effective as standard training programs in improving modifiable cardiovascular risk factors and functional capacity, and could enhance utilization by providing additional options for patients who cannot attend center-based training.^[32,33]^ Indeed, we currently have a trial to test such a model in our setting, which, if proven effective, could also be applied to overcome utilization barriers for our population.^[34]^

In conclusion, through this study, we hope to understand the barriers in our region better, so we can ultimately address them to improve access to secondary prevention care for CVDs. While this is a single-center study, given the similarity of the setting to other centers in East-Central Europe, we hope the results of this work can inform efforts to improve CR access across the region.

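### One comparison is labelled both content and construct validity, and the two tests allowed for it do not fit characteristics with three or more categories

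*Protocol article*

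**What the plan says.** All places are in the protocol article.

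- **Label in 2.9 (Analysis):** "To test construct validity, differences in CRBS total scores will be compared by the sociodemographic and clinical characteristics outlined above".
- **Label in 2.8 (Outcomes):** "differences in barrier scores by some patient characteristics will also be assessed to investigate content validity". The abstract and 2.6 also use the content-validity label. The aims in the Introduction name a third term, design validity.
- **Tests:** for criterion validity, 2.9 states "we will use a *t* test and Pearson correlation, as applicable". For the comparison by characteristics, it states that "differences in CRBS total scores will be compared by the sociodemographic and clinical characteristics outlined above, using the same 2 tests as applicable". The significance threshold is P < .05.
- **Characteristics:** the sociodemographic list in 2.6 includes "age, sex, marital status, highest educational attainment, income, work status". Section 2.8 names those for this comparison: sex, age, travel time, indication, socioeconomic indicators and risk factor burden. It gives a two-group form only for indication.
- **Rationale:** 2.6 says in general terms that many of the variables relate to barriers or to groups that participate less. The Discussion lists groups with lower enrollment and adherence, among them "unemployed and single persons, less educated people, those with lower income, and those that live farther from CR facilities". It also expects long commuting time to be a leading barrier. Neither place states an expected direction of the CRBS score for the test in 2.9.

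**The concern.** Validation of the Czech scale is the study's first aim, so the type of validity that each analysis supports is part of the conclusion. If the label in the abstract, 2.6 and 2.8 is carried into the results, a content-validity claim will rest on group differences in scores, which do not bear on whether the items are relevant, clear and complete.

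The second problem is the closed list of tests. A t test compares two groups, and Pearson correlation needs a numeric or at least meaningfully scored variable. For an unordered characteristic with three or more levels, the analyst must either merge categories or run several t tests. If the merging is chosen after seeing the data, or several t tests are run at an unadjusted .05, the false-positive rate for that characteristic is no longer 5%.

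**Working it through.** **The plan's own figure.** The only calculated figure in the article is the sample size in 2.5: 21 items × 10 participants = 210, which reproduces exactly. It concerns the factor analysis and not this comparison. The expected sample is 300 to 600.

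**Labels side by side**

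| Place | Term for the comparison of scores by characteristics |
|---|---|
| Abstract, Methods | content validity |
| 2.6 Sample characteristics | content validity |
| 2.8 Outcomes | content validity |
| 2.9 Analysis | construct validity |

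The work that does address content is described separately: review by two bilingual experts and a think-aloud pilot in 50 patients covering clarity, relevance and omissions (2.3, results in 2.10), and content analysis of additional barriers (2.9). The known-groups comparison adds nothing to that. It tests whether scores differ between groups as the construct would predict.

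**Do the two tests fit the characteristics named in 2.8?**

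- Sex and indication have two groups, so a t test fits.
- Age and travel time are numeric, so Pearson fits.
- Risk factor burden fits Pearson if it is scored as a count.
- Socioeconomic indicators are the gap. Education is ordinal, so Pearson on category codes assumes equal spacing. Work status is nominal, and so is marital status if it is used. With three or more levels, neither test applies directly.

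**Cost of pairwise t tests.** Assumptions: g equal groups, normal scores, no true difference, every pair tested at .05. The number of pairs is g(g − 1)/2, giving 3, 6 and 10 for g = 3, 4 and 5. The pairs share groups and are not independent, so the chance of at least one P < .05 was simulated (4,000 runs per setting).

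| N | Groups | Any pairwise t test P < .05 | One-way ANOVA P < .05 |
|---|---|---|---|
| 210 | 3 | 0.1325 | 0.0535 |
| 210 | 4 | 0.188 | 0.04725 |
| 210 | 5 | 0.268 | 0.04425 |
| 300 | 3 | 0.11825 | 0.04525 |
| 300 | 4 | 0.20075 | 0.04575 |
| 300 | 5 | 0.288 | 0.04475 |
| 600 | 3 | 0.1325 | 0.0495 |
| 600 | 4 | 0.20475 | 0.05 |
| 600 | 5 | 0.266 | 0.0455 |

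The simulation standard error at 0.05 is √(0.05 × 0.95 / 4000) ≈ 0.0034, so all the ANOVA results are compatible with 5%. The pairwise rate depends on the number of groups and hardly at all on N, so a larger sample does not cure it.

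**The case against.** The strongest reply is that this is a condensed article. Category coding and cut-points are commonly left to a fuller plan. The words *as applicable* leave room for two-group splits, the Discussion already speaks of single and unemployed persons, and indication is already given as two groups. No section says that pairwise testing will be done. All of this is fair, and it makes the error rates above conditional. It does not remove the point that 2.9 names two tests and no third, so a nominal characteristic kept at three or more levels has no suitable method. Nor can an unseen plan reconcile labels that conflict within the published text.

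It is also fair that content validity would not rest on this comparison alone, since the expert review and pilot stand. Factor structure, Cronbach alpha and criterion validity are unaffected.

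A reader might go further and infer that the validity test cannot fail, because no direction or success rule is given. The documents do not support that. With six independent comparisons and no true differences, the chance of at least one P < .05 is 1 − 0.95^6 = 26.5%, so 73.5% of such studies would show nothing. Counting any single significant result as a pass is not a rule found in the article; requiring two gives 3.3%. A real difference can also be missed: at N = 300 with equal groups, a difference of 0.3 SD has 73.8% power. Counting every variable in 2.6 would raise the first figure, but 2.6 and 2.8 both say that only some are used. Directions per characteristic and a success threshold may be left to the full plan, and their absence here is not itself an error.

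**Conclusion.** The point holds in two parts.

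1. The label contradiction is certain from the text. The construct label in 2.9 is the appropriate one; the content label in the abstract, 2.6 and 2.8 is not.
2. The test list is too narrow for socioeconomic characteristics kept at three or more categories. If this were handled by all pairwise t tests at .05, the false-positive rate per characteristic would be about 12-13% for three equal groups, 19-20% for four and 27-29% for five, against about 5% for one-way ANOVA. This assumes equal groups, normal scores and no adjustment. The article states neither the number of categories nor that pairwise tests will be used. With two-group splits fixed beforehand, the inflation does not arise.

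The missing directions are a lesser matter. The article's rationale would allow some to be stated, and doing so would strengthen the test.

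**What to change.** - **Label.** Call the comparison construct (known-groups) validity in the abstract, 2.6, 2.8 and 2.9, align the term in the aims, and draw no content-validity claim from it. Base that claim on the expert review, the pilot and the coding of added barriers.
- **Tests.** In 2.9, use one-way ANOVA (or Kruskal-Wallis) for nominal characteristics with three or more groups and Spearman correlation for ordinal ones. Alternatively, keep the t test and list the two-group splits before the data are analysed.
- **Directions (preferable).** Before analysis, state the expected direction where the article's own rationale supports one, for example a higher score with longer travel time, so that a difference the other way is not counted as support. Not every low-use group in the Discussion should be converted: the scale has a work/time conflicts subscale, on which unemployed or retired patients could plausibly score lower. No particular share of hypotheses met is required.

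The cost is a change of wording and slightly more analysis, with no new data. The drawback is that support for validity becomes harder to claim.
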